### Contingency Plan

Participants who decide to withdraw because of some discomfort experienced with hearing aids or do not undergo a second MRI testing will be retained in the study for baseline MRI analyses only. In addition, intention-to-treat (ITT) analyses will be used for other analyses not involving MRI data.

### Additional Costs and Reimbursements

No costs would be associated with participating in this research project other than transport costs. All participants will be reimbursed Aus $60 to cover these costs after the completion of the 6-month testing protocol.

### Outcomes

#### Assessments for Study

The assessments selected in this study are categorized as follows: hearing assessments, demographic questionnaire, hearing aid benefit questionnaire, cognitive performance, mood and social interaction assessments, and MRI scanning. All participants enrolled in this study will complete these assessments at the baseline and again after 6 months.

##### Hearing Assessments

**Otoscopy and Tympanometry**

Following otoscopy, all participants will undergo tympanometry and acoustic reflex testing to assess the status of the middle ear [47,48].

###### Pure Tone Audiometry in Each Ear

To understand the degree of hearing impairment, and classify participants according to the type of hearing loss, hearing ability will be measured at threshold frequencies of 0.25, 0.5, 1, 1.5, 2, 3, 6, and 8 kHz (air conduction) and 0.5, 1, 2, and 4 kHz (bone conduction) in both ears. The choice of frequency to be tested corresponds to the amplification range of most modern hearing aids and is consistent with the capturing sensitivity at frequencies affected by SNHL and noise-induced damage. Only participants with either mild or moderate SNHL will be included in this study [47,48].

##### Demographics

Data on a variety of demographic variables will be collected to describe the characteristics of study participants.

##### The Abbreviated Profile of Hearing Aid Benefit Inventory

The Abbreviated Profile of Hearing Aid Benefit (APHAB) inventory [49], which is a 10-minute self-assessment inventory, will be used to assess the hearing aid benefit (for normative data, see [50]). The 4 scales of the APHAB will be assessed, namely ease of communication (EC) in favorable environments, ease of communication with background noise (BN), ease of communication with acoustic reverberation (RV), such as listening to sounds in a large room, and aversiveness (AV), which measures negative reactions to environmental sounds such as traffic and alarm bells

The APHAB inventory subscales exhibit acceptable reliability with Cronbach alpha value of .87 (EC), .83 (RV), .82 (BN), and .86 (AV) in unaided conditions, and test-retest correlation coefficients of .80, .65, .71, and .89, respectively [49].

##### Cognitive Assessments

###### The MMSE Questionnaire

MMSE will be used to assess cognition and will be administered to test the cognitive functioning. MMSE is a valid and reliable way of globally assessing a limited range of cognitive functions [51]. This examination will test the following 5 areas of the cognitive function: orientation, registration, attention and calculation, recall, and language. Participants who exhibit a confusion state while completing the MMSE questionnaire will be advised that they cannot be included in the trial and will be advised to see their general practitioner.

###### The Swinburne University Computerized Assessment Battery

The Swinburne University Computerized Assessment Battery (SUCCAB) will be used to assess the cognitive performance. This cognitive test battery will allow the assessment of changes in the cognitive performance of all participants over a period of 6 months. The battery will test contextual memory, immediate recognition, simple reaction time, choice reaction time, congruent stroop, incongruent stroop, spatial working memory, and delayed recognition memory. The reliability and validity testing of this battery has demonstrated that SUCCAB is sensitive to aging and has been shown to be particularly effective for measuring short-term changes in cognition of the elderly [52]. Furthermore, SUCCAB correlates strongly with memory subsets in the Wechsler Adult Intelligence Scales [53].

##### Psychosocial Assessments

###### Depression, Anxiety, and Stress Scale

Depression, Anxiety, and Stress Scale (DASS) is a well-established self-rating mood scale for measuring 3 related negative emotional states of depression, anxiety, and stress. To assess changes in mood in this study, DASS-21, which is a shortened version (21 items) of the full DASS (42 items), will be used [54]. DASS-21 exhibits excellent subscale reliability with Cronbach alpha of .94 for depression, .87 for anxiety, and .91 for stress [55] and has been validated against other well-established measures, including the Beck Depression Inventory, the Beck Anxiety Inventory, and the State-Trait Anxiety Inventory [55].

###### The Berkman-Syme Social Network Index

The Berkman-Syme Social Network Index (SNI) [56] will be used to assess participants’ social interaction and connections with families and friends. In this study, 12 types of social relationships will be assessed, namely relationships with a spouse, parents, parents-in-law, children, other close family members, close neighbors, friends, workmates, schoolmates, fellow volunteers, members of groups without religious affiliation, and religious groups. Although SNI is commonly used in epidemiological research [57], no detailed assessments exist of its reliability, even if the originators reported an overall value of .92 in a 14-week follow-up study of 245 first-year university students [56]. Because SNI relies on self-report, its validity relies on the honesty of participants.

##### Magnetic Resonance Imaging Assessments

###### Speech Processing Task

During fMRI scanning, participants will view a series of human faces (1 male and 1 female actor) that mouth words in blocks (or “epochs”) lasting 16 seconds (1 word per 2 seconds) each. Each block will be one of 4 conditions termed *matched* (MAT), *mismatched* (MIS), *no sound* (NOS), and *control* (CON), preceded and followed by 10-second rest periods, where a fixation cross (“+”) will be displayed. In each of 2 scanning runs, 4 repetitions of each block type (16 total blocks per run) will be presented in a pseudorandom order, each utilizing different word stimuli. The stimulus presentation time for each of the two scanning runs will be 426 seconds (7 minutes 6 seconds); an additional 20 seconds of imaging data will be acquired following the end of the stimulus presentation to allow the hemodynamic response to return to the baseline.

During MAT, the faces will mouth single syllable, high-frequency words (visual stimuli), such as “cat” or “house,” and the corresponding audio input (auditory stimuli) will be played through the headphones. During MIS, the stimuli will remain the same, but the mouthed words and auditory stimuli will be semantically unrelated (eg, “cat” is mouthed but “house” is heard). During NOS, the visual stimuli will be presented but not the auditory stimuli. During CON, the faces will be presented but will not mouth the words; instead, they will simply open and close the mouth without auditory stimuli. All participants will be asked to press a button whenever a face appears to ensure participant attendance to the task.

###### Magnetic Resonance Imaging Scan Acquisition

The MRI scanning session will include the acquisition of 4 different types of scan data while participants lie supine in the scanner wearing MRI-compatible OptoActive headphones (OptoAcoustics). Participants will have either normal or corrected to normal vision using MRI-compatible goggles. These acquisitions will include 2 fMRI scanning runs while participants perform the speech processing task, a high-resolution T1-weighted structural image (∼8 minutes), diffusion-weighted images (∼10 minutes), and a resting state fMRI scanning acquisition (∼10 minutes); the total scanning time will be 42 minutes.

The following details the different scan protocols, including scan parameters, preprocessing, and data analysis:

Scan acquisition for the speech processing task will utilize a T2* sensitive echo-planar imaging sequence (repetition time [TR]=2000 ms; echo time [TE]=30 ms; flip angle=90°; field-of-view=192 mm, 46 interleaved slices, 3-mm^3^ isotropic voxels). Preprocessing and statistical analysis will be performed using SPM12 and associated toolboxes. Preprocessing will include slice-timing correction, motion correction, coregistration of realigned functional images to structural (T1-weighted) scans, warping (“normalization”) of structural and functional scans into standardized stereotactic space, and spatial smoothing of functional images. The data will be modeled by constructing separate regressors that depict the onset and duration of MAT, MIS, NOS, and CON blocks, convolved with the canonical hemodynamic response function supplied with SPM12. Covariates of no interest (eg, image realignment and other noise parameters) will model noise components.Resting state scanning will utilize T2*-weighted images, which will be acquired continuously using an interleaved multiband sequence (multiband acceleration factor=6; bandwidth=1860 Hz/Px; TR=870 ms; TE=30 ms; echo spacing=0.69 ms; flip angle=55°; field-of-view=192 mm; voxel resolution=2 mm x 2 mm x 2 mm; slice-thickness=2 mm; number of slices=66). In addition, multiband acquisition sequences will be derived from the Human Connectome Project [58]. Data analysis will be performed using the “CONN” connectivity toolbox [59] to test changes in the functional connectivity between brain areas we find to be critical in the sensory integration task as a function of wearing the hearing aids, in addition to broader network connectivity. Next, images will be realigned, normalized to a standard stereotactic space defined by the Montreal Neurological Institute (MNI space), spatially smoothed with a 5-mm kernel, and temporally band-pass filtered (0.010-0.100 Hz). T1-weighted images will be segmented into gray and white matter, as well as the cerebrospinal fluid. Then, physiological noise and motion parameters will be regressed from the functional images using ACompCor [60]. Temporal confounds regressed from the time series will include head motion parameters and their temporal derivatives, in addition to ACompCor-derived noise components.The T1-weighted image will be acquired using a magnetization-prepared gradient echo sequence (TR=1900 ms; TE=2.52 ms; flip angle=9°; field-of-view=256 mm x 256 mm; 176 slices; 1-mm^3^ voxels). Diffusion-weighted images will be acquired using an isotropic diffusion tensor imaging sequence for fractional anisotropy (FA) estimations (number of directions=60; *b*-value=3000 s/m^2^; slice-thickness=2.5 mm; TR=8400 ms; TE=117 ms; flip angle=90°). In addition, T1-weighted images will be used in the coregistration of functional data and also perform the analysis of regional brain volumes using voxel-based morphometry (VBM) using DARTEL procedures. For VBM, images will be manually reoriented and segmented [61], then a template will be created from the reoriented images using the nonlinear deformations that best align the segmented images, which will subsequently be warped into stereotactic space and spatially smoothed.Finally, we will perform diffusion-weighted magnetic resonance (MR) white matter tractography using “MRTrix” [62] to assess white matter tract changes as a function of wearing the hearing aids. Preprocessing steps will include constructing a brain mask, estimating diffusion tensor components, and performing constrained spherical deconvolution. Subsequently, we will perform whole-brain and seed-based fiber tracking.

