### Study Objective

Through this study, we seek to understand whether the use of hearing aids can alter the neurocognitive function and affect beneficial plastic brain changes in individuals with SNHL. In particular, we aim to determine whether early intervention can normalize the function of the speech processing brain network. To this end, we will use neuropsychological, clinical, and psychophysical tests in combination with functional and structural MRI (fMRI and sMRI). In addition, fMRI acquisitions will include scanning during the performance of a speech processing task (detailed later) to probe the function of the speech processing network, besides the resting state fMRI to probe the brain network function more generally, whereas sMRI would enable the assessment of both the volume and integrity of the gray and white matter.

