### Primary Statistical Analyses

In this study, repeated measures mixed model group (no hearing aid vs hearing aid users) x Time (Time 1 vs Time 2) analysis (RMMM) will be used for all analyses. The missing data will be accommodated in this analysis; however, in the case of whole-brain fMRI analyses, only completed protocol participants will be included. In the ITT RMMM analyses, the autoregressive (AR) dependence will be assumed.

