##### Structural T1 Data: Structural Alteration

To assess plastic alteration in response to the first-time hearing aid use, these spatially smooth gray matter images will be entered into an RMMM.

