#### Neuroimaging Data

We will explore changes in phoneme and viseme processing separately and their integration, as a function of the hearing aid use by modeling combinations of MAT, MIS, NOS, and CON, in addition to any change in the functional connectivity using the generalized psychophysiological analytic approach [63]. In addition, we will explore the altered whole-brain connectivity and internetwork coupling using the resting state data. Finally, we will assess the white matter alteration using the VBM approach described above for the gray matter. Furthermore, we will plan to explore changes in the white matter integrity using diffusion tensor analyses and diffusion tractography.

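### The gray-matter pipeline is cross-sectional, but its output is used to test 6-month change; a within-person registration step would be a cheap gain in precision

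*Protocol article*

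**What the plan says.** The Study Objective gives the purpose of structural imaging: "sMRI would enable the assessment of both the volume and integrity of the gray and white matter". Under Magnetic Resonance Imaging Scan Acquisition, which announces that it sets out scan parameters, preprocessing and analysis, the T1 images are to be used to "perform the analysis of regional brain volumes using voxel-based morphometry (VBM) using DARTEL procedures". The steps follow in order, beginning with reorientation, segmentation and a group template. The outline then closes with the alignment, warping and smoothing steps: "the nonlinear deformations that best align the segmented images, which will subsequently be warped into stereotactic space and spatially smoothed".

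Under Primary Statistical Analyses, the general model is a "repeated measures mixed model group (no hearing aid vs hearing aid users) x Time (Time 1 vs Time 2) analysis (RMMM"). For the structural data the article says: "To assess plastic alteration in response to the first-time hearing aid use, these spatially smooth gray matter images will be entered into an RMMM". The exploratory Neuroimaging Data section extends the method: "we will assess the white matter alteration using the VBM approach described above for the gray matter".

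No step that registers a participant's two scans to each other is named. Modulation (scaling the warped tissue map by the Jacobian of the deformation) is neither named nor excluded.

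**The concern.** The listed sequence is the one used to compare different people at a single time. Here the quantity of interest is a difference within one person over 6 months, compared between two groups. If each visit's scan is segmented separately and brought to the group template by its own deformation, each visit carries its own segmentation and warping error, and both errors enter the change. A direct registration of the two scans uses the fact that they show the same brain and can remove part of that error.

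What is at stake is precision in a structural analysis listed among the primary analyses, in a study that plans for 27 participants per group at follow-up. The exploratory white-matter analysis inherits the same sequence.

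**Working it through.** The article states no figure for gray-matter change (no SD, effect size or power), so there is nothing to reproduce. The figures in Study Power Analysis concern spatial working memory and are not affected.

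**1. The sections side by side.**
- Scan Acquisition: reorient, segment, build a group template, warp, smooth.
- Structural T1 Data: the images so produced enter the group-by-time model.
- The only alignment described between a person's two visits is therefore through the group template.
- A pairwise longitudinal pipeline registers the two scans first and segments their average. That changes which image is segmented and warped, so it is not merely an unreported setting of the listed steps.

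**2. Effect on precision.** Let r be the between-visit correlation of a voxel or regional value, with equal cross-sectional SD at both visits. Then

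SD(change) / SD(cross-sectional) = sqrt(2(1 − r)).

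The values of r are assumed:

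| r | sqrt(2(1 − r)) |
|---|---|
| 0.90 | sqrt(0.20) = 0.447 |
| 0.95 | sqrt(0.10) = 0.316 |
| 0.98 | sqrt(0.04) = 0.200 |

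- From 0.95 to 0.98: 1 − 0.200/0.316 = 0.37, a 37% smaller SD. The variance ratio is 0.10/0.04 = 2.5, so the gain equals that from 2.5 times the sample size.
- From 0.90 to 0.95: 1 − 0.316/0.447 = 0.29, a 29% smaller SD. The variance ratio is 0.20/0.10 = 2.

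These lines show what a given rise in r would be worth. They do not show how far r would rise in this study.

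**3. Why modulation should be stated.** In a one-dimensional toy model, let a region's true volume change by s, and let the warp absorb a share f of that change. An unmodulated map shows (1 + s)^(1 − f) − 1; a modulated map shows s. With s = −1% and assumed shares:

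| f | Unmodulated | Modulated |
|---|---|---|
| 100% | 0% | −1.0% |
| 80% | −0.20% | −1.0% |
| 50% | −0.50% | −1.0% |
| 0% | −1.0% | −1.0% |

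Modulation would thus matter if it were left out. The table does not show that it is left out.

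**The case against.** The strongest case against the point is that a condensed article's silence is being read as a design. The VBM description is a short outline without a smoothing kernel or template settings, and such detail is commonly left to a fuller document that is not at hand. The article does not say that the two visits are processed independently.

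For modulation this objection succeeds. A reader might infer that the maps are unmodulated, so that real volume change is normalised away and the endpoint does not measure volume at all. The documents do not support that. They declare an analysis of regional volumes by DARTEL, and whether the warp preserves volume is a setting of that step, so the declared aim is compatible with modulation and suggests it.

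For within-person registration the objection succeeds only in part. The section presents itself as setting out the preprocessing and gives the steps in order, and the structural analysis refers back to their output. An analyst following the text would run a cross-sectional sequence. Even so, missing longitudinal registration does not remove the volume signal from modulated maps: volume is measured at each visit and the interaction still tests change. What is lost is precision, with some possibility of registration bias.

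It is also true that the Study Hypotheses name no gray-matter volume hypothesis, that the primary cognitive measure does not involve VBM, and that the white-matter VBM is exploratory. The consequence is confined to the structural aim and its analysis.

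**Conclusion.** The point holds as a worthwhile, inexpensive improvement and not as a failure of the endpoint. As described, the two scans of one person meet only in the group template, and avoidable segmentation and warping error enters each 6-month change. The illustrative gain is a 29% to 37% smaller SD of change. It rests wholly on the assumed rises in r (0.90 to 0.95, and 0.95 to 0.98) and on equal SDs at the two visits; the article supplies none of these. The judgement that volume is still measured at each visit assumes modulated maps, which fits the stated aim but is not written down. No figure in the article changes.

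**What to change.** In the VBM text of Scan Acquisition and in Structural T1 Data, specify the following:

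- Register each participant's baseline and 6-month T1 scans to each other with SPM12's symmetric pairwise longitudinal registration.
- Segment the within-person average and normalise it with DARTEL.
- Enter Jacobian-modulated gray-matter volume maps, or the within-person volume-change map, in the group-by-time comparison. With one change map per person, the between-group difference in change is the interaction.
- State in the same sentence that the maps are modulated, as a clarification in line with the regional-volume aim.
- Use the same approach for the exploratory white-matter VBM.

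No new scan is needed, and SPM12 is already named for the task fMRI. The cost is a revised pipeline description and some computing time. Participants without a second scan do not contribute to the change map, but the Contingency Plan already keeps them for baseline MRI analyses only.

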
###### Auditory Stimuli Input Considerations

As the speech processing task will involve hearing word stimuli, the auditory input for each participant will be tailored to fit a normalized audiogram, that is, the gain will be enhanced at impaired frequencies. This will be performed by fitting a spline function to prerecorded audiograms that will be used to modulate auditory stimuli for the left and right ears separately. Additionally, the headphone output will be modified such that it is consistent across individuals.

### Primary Statistical Analyses

In this study, repeated measures mixed model group (no hearing aid vs hearing aid users) x Time (Time 1 vs Time 2) analysis (RMMM) will be used for all analyses. The missing data will be accommodated in this analysis; however, in the case of whole-brain fMRI analyses, only completed protocol participants will be included. In the ITT RMMM analyses, the autoregressive (AR) dependence will be assumed.

#### Cognitive Data

The SUCCAB performance measure for spatial working memory will be used as the primary SUCCAB measure; this measure has been found to be particularly effective in measuring short-term changes in cognition of the elderly [52] and is calculated by dividing the response accuracy by the reaction time for a spatial working memory task. Using this and other SUCCAB performance measures, baseline values for the 2 groups will be compared using an ANCOVA analysis, controlling for age, gender, and education level. In addition, changes in these values over time will be compared for the 2 groups of respondents using an ITT RMMM, controlling for age, gender, and education level and any variable that differs markedly between the groups at the baseline.

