### Study Hypotheses

In comparison to the long-term hearing aid users, after wearing a hearing aid for 6 months, the group who have never worn a hearing aid will exhibit improved cognition, reduced depression, improved social interaction, altered activation of the auditory cortices and attendant networks, and altered connectivity between auditory and attendant networks.

In addition, the study will explore any baseline relationships among the cognition, psychosocial, and neural function in participants with and without a hearing aid and any relationships among the improved cognition, psychosocial function, and neural function in participants without a hearing aid after the hearing aid intervention, as seen in Figure 1.

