### Study Power Analysis

With 30 consented participants in each group with a significance level of 5%, the power of 80%, and controlling for age, gender, and level of education, the baseline analysis of covariance (ANCOVA) model for spatial working memory performance can detect effect sizes of *d*=0.63 for between-group differences. Allowing 10% attrition in the 6-month follow-up period, a sample size of 27 in each group with a significance level of 5% and power of 80%, a significant group-by-time interaction effect can be detected for a large effect size of *d*=0.77. This study is based on the assumption that an effect size of *d*

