**Neuroimaging Data**

Inferences from functional and structural neuroimaging analyses will be assessed using the random field theory to correct for multiple comparisons at the cluster level.

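### Several outcome domains share the primary heading with no trial-wide primary outcome or testing order, although only spatial working memory is named in the power analysis

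*Protocol article*

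**What the plan says.** The analysis plan has two tiers, *Primary Statistical Analyses* and *Exploratory Analyses*. There is no secondary tier. The primary tier opens with one group-by-time mixed model that "will be used for all analyses", and then takes the domains in turn:

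- **Cognition.** Spatial working memory "will be used as the primary SUCCAB measure". The other SUCCAB measures are analysed in the same way. The SUCCAB section lists eight tasks in all.
- **Mood and social interaction.** DASS and the Social Network Index are tested for change between groups. The DASS section describes three states. The analysis section does not fix whether three scores or one will be used.
- **Imaging.** The two activation contrasts (MAT>NOS and NOS>CON) and the gray matter images each enter a group-by-time model, and connectivity follow-ups are built on the two contrasts. Imaging inference uses "random field theory to correct for multiple comparisons at the cluster level".

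*Study Hypotheses* says that first-time users "will exhibit improved cognition, reduced depression, improved social interaction, altered activation of the auditory cortices and attendant networks", and adds altered connectivity, with no order among these claims.

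*Study Power Analysis* names one outcome, in the baseline "ANCOVA) model for spatial working memory performance can detect effect sizes of" 0.63. It then takes "a sample size of 27 in each group with a significance level of 5% and power of 80"% and gives d = 0.77 for the group-by-time interaction. No other outcome is mentioned there, and the 5% level appears nowhere else in the article.

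**The concern.** The primary label is attached to several domains at once. The single word that could set an order applies only inside SUCCAB. A reader cannot tell whether the trial's main conclusion rests on spatial working memory, on any cognitive measure, on mood, on social interaction or on an imaging map. The random field correction does not help, because it controls error over locations within one map, not across maps or across behavioural outcomes.

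What is at stake is the error rate of the headline conclusion. A 5% level describes one test. If the main claim may be drawn from whichever domain shows a difference, the chance that a null intervention yields a favourable-looking result is larger than that level suggests, and the power calculation no longer describes the claim being made.

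**Working it through.** **1. The plan's own figure.** Inputs from *Study Power Analysis*: 27 per group, 5%, power 80%. Sidedness is not stated; two-sided is assumed.

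Detectable d = (1.960 + 0.842) × √(2/27) = 2.802 × 0.2722 = 0.763 by the normal approximation, and 0.777 by the t-test. Power at d = 0.77 is 80.8% (normal) or 79.3% (t). The stated 0.77 therefore reproduces as a two-sided 5% test of a single outcome, with nothing reserved for other tests.

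**2. Count of tests under the primary heading.**

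- Behavioural: 8 SUCCAB + 3 DASS + 1 SNI = 12. With one DASS score it is 8 + 1 + 1 = 10.
- Imaging maps: MAT>NOS, NOS>CON and gray matter = 3, before any connectivity follow-up.

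**3. Chance of at least one false result, independent tests.** Each test is taken at two-sided 5%, so 2.5% falls in the favourable direction.

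- Favourable direction, 10 tests: 1 − 0.975^10 = 22.4%
- Favourable direction, 12 tests: 1 − 0.975^12 = 26.2%
- Either direction, 10 tests: 1 − 0.95^10 = 40.1%
- Either direction, 12 tests: 1 − 0.95^12 = 46.0%

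The favourable direction is the relevant one for behaviour, because the hypothesis there is directional (better cognition and social interaction, less depression). For imaging the hypothesis says only that activation and connectivity will be altered, so a false positive in a map has no favourable side.

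**4. Allowing for correlation.** Outcomes in the same people are likely to be positively correlated. The article gives no correlations, so 0.3, 0.5 and 0.7 are illustrative. Simulation used equicorrelated normal statistics, 200,000 draws, threshold 1.96:

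| Pairwise correlation | 12 tests, favourable | 12 tests, either | 10 tests, favourable | 10 tests, either |
|---|---|---|---|---|
| 0.3 | 20.2% | 39.7% | 17.9% | 35.1% |
| 0.5 | 16.0% | 32.0% | 14.3% | 28.6% |
| 0.7 | 11.5% | 23.2% | 10.7% | 21.4% |

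For 12 tests, the lowest favourable figure is 11.5 / 2.5 = 4.6 times what one test allows.

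**5. What the remedies do to power** (n = 27 per group, d = 0.77, t-test):

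- Single primary test at 0.05: 79%, detectable d unchanged.
- Bonferroni over all 12 behavioural tests, 0.05/12 = 0.00417: 44%, detectable d about 1.05.
- First Holm step over the 11 behavioural outcomes other than spatial working memory, 0.05/11 = 0.0045: about 45%.

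**The case against.** The strongest case on the other side is that the protocol does single out one measure. Spatial working memory is called primary among the SUCCAB measures, and it is the only outcome in the power analysis, so the other seven SUCCAB measures are plainly ranked below it. The word primary in the heading may mean no more than main as opposed to exploratory. Multiplicity rules for secondary outcomes commonly sit in a statistical analysis plan, which is not shown.

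Much of this stands, and it rules out three stronger readings that a reader might infer:

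- *That about 15 tests are all co-primary.* The SUCCAB wording contradicts this. Twelve behavioural tests is not a floor either, since a single DASS score makes it ten.
- *That a false benefit is nearly as likely as not.* The 46% for 12 tests, or 1 − 0.95^15 = 54% with the three maps added, counts errors in either direction under independence. A false benefit needs the favourable direction, which is much less likely.
- *That any one of these tests would confirm the hypothesis.* Anxiety, stress and gray matter are not in the hypothesis, its claims are joined by *and*, and the article nowhere says that one success is enough.

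The objection does not remove the point. The article is not silent and leaving the matter to a later document: it assigns the primary label itself, to several domains. Nothing ranks spatial working memory above mood, social interaction or imaging. Timing matters too. *Results* schedules baseline analyses to finish by October 2019, before follow-up ends in December 2020. A primary outcome chosen later could therefore be chosen after the baseline comparison of these non-randomised groups has been seen.

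**Conclusion.** The point holds as one of labelling and hierarchy. The protocol groups several domains as primary, names no outcome as primary for the trial, gives no testing order, and corrects for multiplicity only within imaging maps.

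Without a hierarchy, the chance of at least one false favourable behavioural result is about 22% to 26% for 10 to 12 independent tests. For 12 tests it is about 12% to 20% at correlations of 0.7 to 0.3. One test allows 2.5%.

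These figures rest on four assumptions: every behavioural test is done at two-sided 5%, which the article states only in the power analysis and without sidedness; no true effect exists on any outcome; the correlations are illustrative; and a favourable result in any domain would be presented as support. They measure the room that the wording leaves, not an error rate to which the plan commits itself. The point merits correction, and the correction is simple because the measure already powered can take the primary role.

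**What to change.** In *Primary Statistical Analyses* and its *Cognitive Data* subsection, name the group-by-time effect on spatial working memory as the single primary test of the trial at two-sided 5%. This matches the power analysis and leaves d = 0.77 as it is.

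Add a secondary tier with two families: behavioural (the other seven SUCCAB measures, DASS with its scoring fixed, and SNI) and imaging (MAT>NOS, NOS>CON, gray matter and the planned connectivity analyses). Apply Holm or false-discovery-rate control within each family, and keep the random field correction inside each map. Leave the analyses now under *Exploratory Analyses* as they are.

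The change is to wording only, but strict adjustment is not cheap for individual secondary outcomes. At the first Holm step over 11 outcomes, power at d = 0.77 falls from about 80% to about 45%. False-discovery-rate control, or unadjusted secondary results clearly labelled as such, is an acceptable alternative once the single primary test is fixed.
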